### Intervention scheme / trial flow

Inpatients from all trial sites that meet the inclusion criteria and give informed consent are consecutively included into the trial within one week after admission. After inclusion, inpatients will be interviewed by the blinded research psychologist. Initial self-report measurements and objective data in relation to depression and associated co-morbidity as well as medication are assessed by a trained diagnostician. In addition, treatment expectancy and responsibility to seasonal effects will be assessed. After the pre-treatment assessment (T1), patients are randomized to either a placebo control condition (PCC) or BLT. Both groups also receive TAU. Trial interventions will be delivered each morning (except weekends) over a period of four weeks about 7.5 h after the DLMO assessed with the MEQ.

During the intervention trial, an interim assessment with the BDI-II after two weeks will take place in order to control patient-perceived changes in depression more closely. There is no full assessment in order to reduce stress for the patients. Four weeks after completion of the treatment, individuals will again be interviewed by the blinded research psychologist and score the self-rating questionnaires as well as perform the neuropsychological assessment and deliver saliva melatonin and cortisol (post-treatment assessment; T2). Three and six months after T2, follow-up assessments will be performed via telephone and questionnaires to control for stability (T3 and T4). There is no full reassessment for neurobiological and neuropsychological data in order to facilitate the response to fulfil the follow-up assessment and to meet patients’ needs best. Moreover, AEs will be assessed in both treatment groups on a weekly basis. For an overview of the trial flow, see Fig. 1. For details on procedures per time point, see Figs. 2 and 3.

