**Fig. 1 Fig1:**
[figure not shown]
Trial flow overview. PCC placebo control condition + TAU, BLT Bright Light Therapy + TAU; T1 assessment before treatment, T2 assessment at the end of the four-week treatment, T3 follow-up after three months

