### Measurements

The primary endpoint of the study is the change in patient-perceived severity of depressive symptoms after treatment, assessed with the BDI-II.

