#### Children’s Depression Rating Scale-Revised (CDRS-R)

Clinician-rated reduction of depressive symptoms, assessed by a blinded investigator after four weeks of treatment (at T2). The CDRS-R ([35, 36]) is a widely used semi-structured interview to assess clinician-rated depressive symptoms. It has been applied in various multicenter studies to assess efficiency of pharmacotherapy and psychotherapy in adolescents (e.g. TADS, [37]; ADAPT, [38]). It shows good psychometric properties (Cronbach’s Alpha = 0.85; inter-rater reliability = 0.92).

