#### Statistical analyses

The primary analysis population is the intention-to-treat (ITT) population comprising all randomized patients. Group difference in change of BDI-II rating under trial treatment will be analyzed by an analysis of covariance (ANCOVA) comprising the covariates baseline BDI-II rating, treatment group, prior pharmacological antidepressant therapy (yes/no), and sex. Missing values will be replaced by multiple imputation. The two-sided level of significance will be α = 5%. Supportive analyses are planned for the Per Protocol Population and the Completer Population. The Per Protocol Population comprises all patients from the ITT population without major protocol violations: lack of compliance with regard to therapy sessions; not meeting all inclusion criteria; meeting at least one exclusion criterion; intake of unallowed concomitant medication during the study; end of treatment visit out of schedule. In an additional sensitivity analysis, missing values will be analyzed based on the last available BDI-II rating (Last Observation Carried Forward [LOCF]). In case the LOCF approach turns out to be not conservative, an additional Baseline Observation Carried Forward (BOCF) analysis will be performed.

Further subgroup analyses are planned to detect possible differences between predictive factors (e.g. trial site, concomitant psychotropic medication for co-morbid disorders, baseline CAR and DLMO, type of depression [seasonal/non-seasonal], season, expectancy questionnaire). No interim analyses are planned. Secondary endpoints will be analyzed descriptively applying appropriate methods depending on the scale of the respective parameter. Interpretation of statistical tests must be exploratory except for the primary outcome.

AEs will be coded according to MedDRA terminology. Detailed information collected for each AE will include: a description of the event; duration; whether the AE was serious; intensity; relationship to trial treatment; action taken; and clinical outcome. Summary tables will present the number of participants observed with AEs by MedDRA System Organ Class and Preferred Term and corresponding percentages. Additional subcategories will be based on event intensity and relationship to trial treatment. A subject listing of all AEs will be prepared.

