## Abbreviations

ANCOVA: Analysis of covariance
BDI-II: Beck Depression Inventory II
BLT: Bright light therapy
BOCF: Baseline Observation Carried Forward
CAR: Cortisol awakening response
CDRS - R: Children’s Depression Rating Scale – Revised
CGI-I: Clinical Global Impression-Improvement
CGI-S: Clinical Global Impression-Severity
CHIP – AE: Child Health and Illness Profile-Adolescent Edition
DALYs: Disability Adjusted Life Years
DGKJP: German Association for Child and Adolescent Psychiatry
DLMO: Dim light melatonin onset
HRQoL: Health-related quality of life
ICH-GCP: International Council for Harmonization of Technical Requirements for Pharmaceuticals for Human Use (ICH) - Good Clinical Practice
ITT: Intention-to-treat
IZKS: Interdisziplinäres Zentrums Klinische Studien
KIGGS: Studie zur Gesundheit von Kindern und Jugendlichen in Deutschland
LOCF: Last Observation Carried Forward
MedDRA: Medical Dictionary for Regulatory Activities
MEQ: Morningness–Eveningness Questionnaire
NICE: National Institute for Health and Care Excellence
PCC: Placebo control condition
SAD: Seasonal affective disorder
SAE: Serious adverse events
SDQ: Strengths and Difficulties Questionnaire
SF-B/R: Schlaffragebogen B – Revidierte Fassung
SPAQ: Seasonal Pattern Assessment Questionnaire
T1: Pre-treatment assessment
T2: Post-treatment assessment after four weeks
T3: Post-treatment assessment after three months
T4: Post-treatment assessment after six months
TADS: Treatment of adolescents with depression study
TAP: Testbatterie zur Aufmerksamkeitsprüfung
TAU: Treatment as usual
TORDIA: Treatment of resistant depression in adolescents
UKE: Universitätsklinikum Hamburg-Eppendorf

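### The trial-flow text puts T2, the visit that supplies the primary outcome, four weeks after treatment ends, while the Fig. 1 caption and the CDRS-R section put it at the end of treatment

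*Protocol article*

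**What the plan says.** All places are in the protocol article.

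- **Intervention scheme / trial flow** gives the length of treatment: "Trial interventions will be delivered each morning (except weekends) over a period of four weeks". It then describes the next full assessment: "Four weeks after completion of the treatment, individuals will again be interviewed by the blinded research psychologist". The same sentence goes on to the questionnaires, neuropsychology and saliva samples, and ends by naming the visit: "deliver saliva melatonin and cortisol (post-treatment assessment; T2". T3 and T4 follow three and six months after T2.
- **Fig. 1 caption**: "T2 assessment at the end of the four-week treatment".
- **CDRS-R section**: "assessed by a blinded investigator after four weeks of treatment (at T2".
- **Abbreviations**: "T2: Post-treatment assessment after four weeks", without saying what the four weeks are counted from.
- **Measurements** defines the primary endpoint as "change in patient-perceived severity of depressive symptoms after treatment, assessed with the BDI-II". No week or visit is named.
- **Statistical analyses** sets the primary comparison: "Group difference in change of BDI-II rating under trial treatment". Its list of major protocol violations also refers to a visit at the end of treatment.

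**The concern.** T2 is the only full assessment between baseline and the three-month follow-up, so it is the visit that supplies the primary BDI-II score. The document schedules it at two times that cannot both be right.

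The choice decides what the trial estimates. A score at the end of treatment measures the effect of light while it is being given. A score four weeks later measures what is left after light has stopped. The other outcomes collected at T2 (CDRS-R, CGI-I, alertness, melatonin and cortisol) change meaning in the same way. Once data have been collected at the wrong time, an analysis plan cannot put them right.

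**Working it through.** **1. The plan's own figure.** The sample size is reproduced first, to see whether the time point enters it.

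- Inputs (sample size section): pilot remission 46.7% and 25.9%, SD 10, target difference 4.37 points, independent t-test, 5% significance level (two-sided in the statistical section), power 90%.
- Cohen's h = 2·arcsin(√0.467) − 2·arcsin(√0.259) = 0.437. With SD 10 this becomes 4.37 points.
- The t-test solution for d = 4.37/10 = 0.437 is 111.01 per arm. Rounded up, this is 112 per arm and 224 in total, as stated. Power at 112 per arm is 0.903.

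The calculation has no term for the visit date, so the contradiction does not change it.

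**2. The calendar.** Week 0 is the first session and treatment is taken as four calendar weeks. Three months is taken as 13 weeks and six months as 26.

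| Visit | T2 at end of treatment (Fig. 1 caption, CDRS-R) | T2 four weeks after completion (trial-flow text) |
|---|---|---|
| Last session | about week 4 | about week 4 |
| T2 | about week 4 | 4 + 4 = about week 8 |
| T3 | 4 + 13 = week 17 | 8 + 13 = week 21 |
| T4 | 4 + 26 = week 30 | 8 + 26 = week 34 |

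The two readings differ by four weeks at every visit from T2 on.

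**3. What the BDI-II covers on each reading.** The Measurements section says that the instrument asks about the last seven days. At week 4 those are the final days of treatment. At week 8 they are roughly days 50 to 56, and treatment ended at about day 28. That window contains no treatment day and opens about three weeks after the last one.

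**4. Which reading the other sections support.**

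- Fig. 1 caption: end of treatment, explicitly.
- CDRS-R section: end of treatment, explicitly.
- Statistical analyses: change during treatment and an end-of-treatment visit. Both fit week 4; neither fits week 8.
- Primary endpoint: change after treatment. Compatible with both.
- Abbreviations: after four weeks. Compatible with both.
- Trial-flow text: four weeks after completion, explicitly.

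One sentence stands against two explicit statements and the analysis wording.

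**5. The link from T2 to the primary endpoint.** The endpoint definition does not name T2. The link rests on T2 being called the post-treatment assessment and being the only full one before the follow-ups. The inference is sound, but the reader has to make it.

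**The case against.** The strongest reply is that this is a drafting slip. The sentence was probably meant to say that patients are seen again on completing the four weeks, and the rest of the document shows the intention. Much of this stands: it would be too strong to say that nothing in the document settles the matter. It does not remove the point. The faulty sentence is in the section that describes how the trial runs, and a delayed visit is not an absurd reading, since the pilot also measured its outcome three weeks after light had ended.

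A second reply is that Figs. 1 to 3, one of which lists the time points of visits, are not reproduced in the text at hand, and that a fuller protocol may state the week. That is fair, and it rules out claims about what sites would actually do. It does not reconcile a legible caption with the paragraph that refers to it.

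A reader might infer more than the document supports:

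- **Loss of power at week 8.** No rate of fading is given. The 4.37-point target was itself derived from pilot remission three weeks after light ended, so discounting it for time off light has no basis.
- **Sites following different dates, or T2 usually falling after discharge.** Nothing in the document shows either. No length of stay is stated.
- **A per-protocol visit criterion that cannot be applied.** The criterion names the end-of-treatment visit, and its window may properly be left to the analysis plan.
- **The abbreviation list as a further vote for week 4.** Its wording fits both readings.

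**Conclusion.** Wrong as written. The visit that supplies the primary outcome is stated at two times four weeks apart, about week 4 and about week 8, and the follow-ups counted from it shift by the same amount. End of treatment is the better supported reading, because the Fig. 1 caption, the CDRS-R section and the statistical section all agree with it. Followed literally, the trial-flow sentence would replace the effect under treatment with persistence after stopping.

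This rests on two assumptions: that T2 supplies the primary BDI-II score, which is inferred, and that treatment lasts four calendar weeks. A reader might conclude that the primary endpoint is undefined or the trial underpowered. Neither follows: the document leans clearly to one date, and the planned 224 patients reproduce from their own inputs.

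**What to change.** 1. In the trial-flow section, correct the sentence so that T2 takes place on completion of the four-week treatment, in line with the Fig. 1 caption, the CDRS-R section and the statistical section.
2. In Measurements, define the primary endpoint as the change in BDI-II from T1 to T2.
3. Count T2 from the patient's actual last session. The Interventions section prolongs treatment for missed days, so a date counted from the first session could fall before treatment is finished.
4. Leave T3 and T4 at three and six months after the corrected T2.

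The cost is two corrected sentences and a short note to the sites. No visit, patient or recalculation is added.

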**Fig. 1 Fig1:**
[figure not shown]
Trial flow overview. PCC placebo control condition + TAU, BLT Bright Light Therapy + TAU; T1 assessment before treatment, T2 assessment at the end of the four-week treatment, T3 follow-up after three months

**Fig. 2 Fig2:**
[figure not shown]
Study process schedule (according to SPIRIT guidelines). T1 pre-treatment assessment, T2 post-treatment assessment, T3 follow-up three months after T2, T4 follow-up six months after T2, BDI-II Beck Depression Inventory II, CDRS-R Children’s Depression Rating Scale-Revised, CGI-S Clinical Global Impression-Severity, CGI-I Clinical Global Impression-Improvement, SPAQ Seasonal Pattern Assessment Questionnaire, SF-BR Sleep Questionnaire-B/Revised, KIDSCREEN10 Health Related Quality of Life self-rating assessment – short version, CHIP-AE Child Health and Illness Profile-Adolescent Edition, SDQ Strength and Difficulties Questionnaire, TAP Testbattery for Attentional Performance; ^a^only subdomain physical activity administered; ^b^ only Alerteness subtest administered

**Fig. 3 Fig3:**
[figure not shown]
Overview of time-points of visits and procedures per time-point

### Measurements

The primary endpoint of the study is the change in patient-perceived severity of depressive symptoms after treatment, assessed with the BDI-II.

#### Beck Depression Inventory-II

The BDI-II is a self-rating instrument that is extensively used in clinical studies worldwide to assess the degree of depressive symptoms of the last seven days (validated in German adolescents; [33]). The score is easily calculated as a sum score. This score will be used in a dimensional way in the analysis, as this provides more power than a categorical use. According to NICE guidelines, the clinically relevant difference between treatment groups is 3 BDI-II scale points. The BDI-II standard deviation is expected to be about 10 scale points. The study aims to show the same treatment differences as in our pilot study [21] of about 4.37 scale points, which is clearly a relevant treatment difference.

The secondary endpoints include independent evaluator-, adolescent-, parent-, and clinician-rated measures of depression, improvement and impairment, and functional status. In addition, measures are included to allow the exploratory examination of a focused set of putative moderators and mediators of treatment response, including demographics, treatment and medical history, diagnostic-level data for depression and co-morbid conditions, scalar measures of internalizing and externalizing symptoms, family functioning and environment, peer relations, academic and school performance, quality of life, and treatment-related expectancies and beliefs:

#### Clinical Global Impression (CGI)

Blinded assessment of the global severity of the symptoms (CGI-S) at baseline and global change in degree of illness compared to the baseline dichotomized at much improved or better on the Clinical Global Impressions-Improvement (CGI-I) scale [34] rated by an experienced blinded clinical investigator.

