### Data analysis

#### Proposed sample size/power calculations

In our pilot study [20], a similar trial design was used, investigating the effects of BLT versus placebo light therapy after a treatment period of 14 days and a follow-up period of three weeks. Remission rates at the end of follow-up (week 5) were 46.7% for BLT and 25.9% for dim light. These remission rates were transformed (2*arcsin; √remission rate). The difference between the transformed remission rates resulted in Cohens h of 0.437 and was used for the calculation of the study sample. A significant difference between the two groups is defined as 3 points on the BDI-II by the NICE guidelines. A standard deviation of 10 points in the BDI-II is assumed. Thus, the proposed study aims to show a group difference of 4.37 points on the BDI-II. Calculations based on this difference yield a sample size of 224 patients (112 for each group) when using an independent t-test at a significance level of 5% and a power of 90%. Sample size was calculated using PROC POWER in SAS® Version 9.4. Drop-outs will be analyzed using multiple imputation methods.

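### The CGI-I is described only as a yes/no responder outcome; an ordinal comparison beside it would recover roughly 7 to 17 points of power under assumed inputs

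*Protocol article*

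**What the plan says.** The Clinical Global Impression section of the protocol article gives the CGI-I outcome as "global change in degree of illness compared to the baseline dichotomized at much improved or better on the Clinical Global Impressions-Improvement (CGI-I) scale", rated by a blinded clinical investigator. Severity (CGI-S) is rated at baseline. No ordinal use of the CGI-I appears elsewhere.

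For the self-rated primary outcome, the Beck Depression Inventory-II section takes the other course: "This score will be used in a dimensional way in the analysis, as this provides more power than a categorical use".

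The Statistical analyses section says of the secondary outcomes: "Secondary endpoints will be analyzed descriptively applying appropriate methods depending on the scale of the respective parameter". It adds that tests other than the primary one are exploratory. Responder status is listed as a secondary objective in the Abstract and at the end of the Background. The CDRS-R section describes a second blinded clinician-rated measure at T2 and states no cut for it.

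**The concern.** The CGI-I is an ordered rating of change. Once it is cut at a single point, every grade below the cut counts the same and every grade at or above it counts the same. The protocol's own argument for the BDI-II, that a dimensional score has more power than a categorical one, points the same way for an ordered clinician rating. The CGI-I section gives no reason to treat it differently.

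The general sentence on choosing methods by scale does not clearly restore the lost information, because the parameter as described is already binary. The primary outcome is self-rated, so the blinded clinician ratings are the natural corroboration. What is at stake is how precisely one of those two ratings can show a group difference.

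**Working it through.** **Inputs stated in the protocol.** 112 per arm, 1:1, two-sided 5%; BDI-II difference 4.37 and SD 10; pilot remission rates 46.7% and 25.9%.

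**Inputs assumed, because the protocol gives none for the CGI-I.** A normal latent scale, the size of the shift on it, seven grades with assumed control-arm frequencies, the control responder rate, and no dropout.

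**Step 1: reproduce the planning figures.** The protocol says "the proposed study aims to show a group difference of 4.37 points on the BDI-II" and "A standard deviation of 10 points in the BDI-II is assumed", so d = 4.37/10 = 0.437. The non-central t distribution gives power 0.89997 with 111 per arm and 0.9025 with 112, so 112 per arm and N = 224 reproduce. The source of the figure also reproduces: h = 2·asin(√0.467) − 2·asin(√0.259) = 0.437. So 0.437 began as an effect size for two proportions ("The difference between the transformed remission rates resulted in Cohens h of 0.437 and was used for the calculation of the study sample") and was then used as a standardised BDI-II difference. It was never set for the CGI-I.

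**Step 2: yes/no comparison at a latent shift of 0.437.** With control responder rate p_C, the treated rate is p_T = Φ(Φ⁻¹(p_C) + 0.437). With n = 112, Δ = p_T − p_C and p̄ the mean rate,

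power = Φ{[Δ − 1.96·√(2p̄(1−p̄)/n)] / √([p_C(1−p_C) + p_T(1−p_T)]/n)}.

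For p_C = 0.259: p_T = 0.417, Δ = 0.158 and p̄ = 0.338. The standard errors are 0.0632 (null) and 0.0623 (alternative), so (0.158 − 0.1239)/0.0623 = 0.547 and power is 0.708.

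**Step 3: ordinal comparison at the same shift.** Tie-corrected Wilcoxon test, 20,000 simulated trials per row. Control-arm frequencies run from the worst to the best grade, and the last two grades are the responders.

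| Control responders | Assumed frequencies | Yes/no | Ordinal | Gap (points) |
|---|---|---|---|---|
| 26% | .01 .03 .08 .25 .371 .209 .05 | 0.708 | 0.866 | 16 |
| 35% | .005 .02 .06 .22 .345 .27 .08 | 0.734 | 0.867 | 13 |
| 35%, coarser spread | .001 .004 .015 .25 .38 .30 .05 | 0.734 | 0.852 | 12 |
| 50% | .005 .015 .04 .14 .30 .37 .13 | 0.731 | 0.858 | 13 |
| 65% | .005 .01 .03 .085 .22 .43 .22 | 0.678 | 0.852 | 17 |

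A separate simulation (8,000 trials per scenario, a separate set of assumed spreads) gave 0.706, 0.747, 0.734 and 0.717 for the cut at control rates of 26%, 40%, 50% and 60%. The rank test gave 0.873, 0.871, 0.867 and 0.863. The gaps are 17, 12, 13 and 15 points. At more extreme control rates the gap widens: 0.626 against 0.868 at 15% (24 points), and 0.604 against 0.836 at 75% (23 points).

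**Step 4: the pilot rates read as responder rates.** The latent shift is Φ⁻¹(0.467) − Φ⁻¹(0.259) = 0.564. The yes/no test has power 0.905 and the rank test 0.974, a gap of 7 points. The separate simulation gave 0.902 against 0.979, a gap of 8.

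**Step 5: why the gap shrinks in step 4.** Both tests are near the ceiling there. Convert power to relative efficiency as ((1.96 + z_cut)/(1.96 + z_ordinal))². Step 4 gives ((1.96 + 1.308)/(1.96 + 1.939))² = 0.70. The 26% row of step 3 gives ((1.96 + 0.548)/(1.96 + 1.108))² = 0.67. In both cases the cut keeps roughly two thirds to 70% of the ordinal information.

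**The case against.** The case against is substantial, and most of it stands.

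- **The cut serves a stated objective.** Responder status is a secondary objective, and at least much improved on the CGI-I is the only responder definition the article appears to give. The binary summary therefore belongs in the plan.
- **No CGI-I test is specified.** Secondary endpoints are descriptive and exploratory, so the two-proportion test in the working is supplied here and is not the trial's.
- **The article is condensed.** It does not expressly forbid tabulating or comparing the grades. It does state the binary form and no other, which is why the point survives as a suggestion.
- **There is no contradiction.** A reader might infer that the CGI-I section conflicts with the BDI-II section. It does not: the power argument is made for the one powered endpoint, and a dimensional primary with a categorical responder secondary is coherent. The argument supports the direction of the point and no more.
- **The larger range is not the trial's own figure.** A reader might infer that the comparison loses 12 to 17 points at the trial's planning effect. The 0.437 is a BDI-II figure derived from remission rates, and those same rates, read as responder rates, give about 90% power for the cut and a gap of only 7 to 8 points.

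What remains is that grades already recorded would be compared less precisely than they could be.

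**Conclusion.** The point holds as a minor efficiency improvement. The CGI-I is described only in binary form. Under the assumptions listed, a yes/no comparison has roughly 7 to 17 points less power than an ordinal one: 7 to 8 at the pilot rates, and 12 to 17 at a latent shift of 0.437 with control responder rates of about 26% to 60%. The figures move with the grade frequencies, the control rate and any dropout, none of which the protocol gives for the CGI-I.

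Two stronger readings are not supported. First, nothing here weakens the primary analysis or the sample size, which reproduces. Second, it would go too far to say that a BDI-II gain would be left without clinician support, because the blinded CDRS-R has no stated cut. Nor is there a case for replacing the responder endpoint.

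**What to change.** Keep the CGI-I responder proportion per arm at T2 and report the difference with its 95% CI. Beside it, in the Clinical Global Impression and Statistical analyses sections or in the analysis plan, add an exploratory between-group comparison of all CGI-I grades at T2. One suitable form is a proportional-odds model adjusted for baseline CGI-S and the stratification factors (prior antidepressant therapy, site, sex), reported as a common odds ratio with 95% CI. A rank test can be used if proportional odds is doubtful. The power figures above come from unadjusted tests, so they indicate what the ordinal scale gains and do not measure this particular model.

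The change needs no new data, visits or patients. Its costs are one more exploratory analysis, the proportional-odds assumption, and an effect measure less familiar to clinicians than a responder rate. The retained proportion covers the last of these.
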